**Fig. 1 Fig1:**
[figure not shown]
Ferric citrate inhibits two stimuli of FGF23 production, dietary phosphate absorption and iron deficiency. Lowering circulating FGF23 concentrations may prevent the development of various FGF23-associated, off-target, adverse effects

### Fibroblast growth factor 23

FGF23 is an essential hormone secreted mainly by osteocytes that physiologically regulates phosphate and 1,25-dihydroxyvitamin D (1,25(OH)_2_D). FGF23 decreases expression of the type II sodium-phosphate cotransporters (NaPi-2a and NaPi-2c) in renal proximal tubules, reducing renal phosphate reabsorption [18, 19]. FGF23 also decreases expression of renal 1α-hydroxylase, the enzyme that converts 25(OH)D to active 1,25(OH)_2_D, and increases expression of renal 24-hydroxylase, the enzyme that converts 25(OH)D and 1,25(OH)_2_D to inactive metabolites, thus decreasing overall renal 1,25(OH)_2_D production [20–22]. Decreased renal phosphate reabsorption and decreased 1,25(OH)_2_D-mediated enteral phosphate absorption results in decreased serum phosphate concentrations. Therefore, in the setting of phosphate loading or hyperphosphatemia, an increase in circulating FGF23 levels directly induces phosphate excretion and indirectly reduces dietary phosphate absorption, thus maintaining normal circulating phosphate concentrations. In the setting of CKD, bone [23] and circulating [7, 8, 24, 25] levels of FGF23 increase early and continue to increase as kidney function declines [7, 8, 24–26], helping to maintain normophosphatemia until late-stage CKD [7, 8].

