### FGF23 production

Given the possible multisystemic adverse effects of increased FGF23 concentrations in CKD, it can be hypothesized that lowering FGF23 levels in patients with CKD may improve clinical outcomes. One potential mechanism to lower FGF23 levels is to target the stimuli that increase FGF23 production. Multiple factors stimulate FGF23 production, central among which is dietary phosphate absorption [14, 15]. In studies of healthy volunteers, a phosphate-depleted diet decreased circulating FGF23 concentrations [14, 15], and a phosphate-loaded diet increased circulating FGF23 concentrations [15].

Recently, iron deficiency has been identified as a novel stimulus of FGF23 production. Several murine studies demonstrate that iron deficiency potently induces *Fgf23* mRNA expression [41–44]. Iron deficiency also concurrently increases intracellular FGF23 post-translational proteolytic cleavage, resulting in secretion of FGF23 protein fragments from the cell [41–44]. However, in CKD, FGF23 proteolytic cleavage may be impaired [45–47], thus uncoupling iron deficiency-induced increased FGF23 transcription from its post-translational cleavage. Therefore, in the *absence* of CKD, iron deficiency results in increased circulating concentrations of FGF23 fragments; however, in the *presence* of CKD, iron deficiency may increase concentrations of full-length FGF23. Indeed, in a pre-clinical study of mice with and without experimental CKD fed an iron-deficient diet, whole bone *Fgf23* mRNA expression and plasma concentrations of total (intact + fragmented) FGF23 increased to a similar degree in both the non-CKD and CKD groups, but the increase in plasma concentrations of full-length, intact FGF23 was much greater in the mice with CKD [44]. The median percentage of circulating FGF23 that was intact was only 12% in the non-CKD iron-deficient mice, but was 72% in the CKD iron-deficient group [44]. Therefore, iron deficiency, which is common in pediatric patients with CKD [48, 49], may represent a novel factor contributing to elevated intact FGF23 levels in CKD.

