For human samples, there are commercial assays to measure both C-terminal FGF23 and intact FGF23 [50]. The C-terminal assay captures both intact FGF23 and C-terminal FGF23 fragments, thus measuring total (intact + fragmented) FGF23 concentrations. Conversely, the intact assay captures only intact FGF23 (iFGF23). In human CKD cohorts, iron deficiency is associated with increased concentrations of circulating total FGF23, as measured by the C-terminal FGF23 assay [51, 52]. Associations between iron status and intact FGF23 levels have not been specifically evaluated in large CKD cohorts; however, given that FGF23 cleavage is impaired in CKD [45–47], it is hypothesized that iron deficiency in CKD would increase intact FGF23 to a greater degree than iron deficiency in the absence of CKD would. In the FIT4KiD trial, the primary outcome is changes in iFGF23, as this is considered to be the biologically active FGF23 moiety, but total FGF23 concentrations will also be measured as an exploratory analysis.

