**Secondary endpoints**
Compared to placebo, from baseline, active therapy with FC will be associated with: -Increased hemoglobin -Increased serum transferrin saturation -Increased serum ferritin -Increased serum 1,25-dihydroxyvitamin D -Decreased serum parathyroid hormone

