**Exploratory endpoints**
Compared to placebo, from baseline, active therapy with FC will be associated with: -Smaller decrease in estimated glomerular filtration rate -Decreased bone FGF23 -Increased osteoid thickness -Decreased biomarkers of bone turnover -Decreased phosphaturia -Increased serum calcium -Increased serum klotho -Decreased serum C-terminal (total) FGF23

**Table 4 Tab4:** Participant inclusion and exclusion criteria

Inclusion criteria
Ages 6 to 17 years (inclusive)
Estimated glomerular filtration rate of 15–59 ml/min/1.73 m^2^ by the updated CKiD formula [60]
Serum phosphate within age-appropriate normal ranges
Serum ferritin < 500 ng/ml and transferrin saturation < 50%
For those patients treated with nutritional vitamin D, calcitriol, iron, and/or erythropoiesis-stimulating agents, doses must be stable for at least 2 weeks prior to screening
Able to swallow tablets
Able to eat at least two meals a day
In the opinion of the investigator, willing and able to follow the study treatment regimen and comply with the site investigator’s recommendations

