**Fig. 2 Fig2:**
[figure not shown]
The Ferric Citrate and Chronic Kidney Disease in Children (FIT4KiD) trial schema. The FIT4KiD study is a randomized, double-blind, placebo-controlled, 12-month trial of 160 pediatric patients with CKD stages 3–4. It will test the hypothesis that, compared to placebo, ferric citrate will safely lower intact FGF23 levels. The study design includes a screening visit, baseline assessments, and post-randomization scheduled follow-up. Further details are provided in Table S1

The primary analyses for this trial will evaluate changes from baseline in iFGF23 concentrations over 12 months between the treatment arm and the placebo arm. The analysis will use a linear mixed-effects model, with random participant effects accounting for repeated measurements, and random site effects accounting for clustering of participants into study sites. The model will include terms for treatment, time, treatment by time interaction (primary term for the inference in this study), baseline iFGF23, and stratification factors (study site, CKD stage, and urine protein/creatinine ratio) as covariates. Time will be modeled as two periods, months 1–3 and months 6–12, with the primary test based on the difference between treatment arms during the second time period [54]. A single interim analysis will be performed at 50% completion of 3 months of treatment or the first quarter of year 3 of the trial. The O’Brien/Fleming rules for interim analysis were used, assigning an alpha of 0.0054 to the midpoint analysis, and 0.0492 to the final analysis [59].

To evaluate the power of the trial, we carried out a simulation study using the analysis approach described above. Simulated data sets were created assuming that the mean level of natural log-transformed iFGF23 is the same at baseline in both arms, changes linearly during the first 3 months, is stable from 3 to 12 months in the treatment arm, and remains constant over time in the placebo group, as previously reported [54]. We utilized data from the CKiD cohort to estimate the design parameters (baseline mean, between sites and within and between subjects standard deviations) for the simulation. The simulation also assumed that 20% of participants would be lost to follow-up by month 12. The results of our simulation study showed that a sample size of 160 participants provides 80% power to detect a treatment difference of 26% between treatment vs. placebo.

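### Baseline iron status, already measured for eligibility and named as a target of the drug, is not a covariate in the primary model; adding transferrin saturation could buy a small amount of precision at almost no cost

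*Protocol article*

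**What the plan says.** The primary-analysis paragraph after Fig. 2 (section The FIT4KiD trial) describes a linear mixed model for iFGF23. It has treatment, time, their interaction, and "baseline iFGF23, and stratification factors (study site, CKD stage, and urine protein/creatinine ratio) as covariates". The primary test compares the arms in months 6–12. Neither the stratification factors nor the other covariates include ferritin, TSAT or iron therapy.

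Elsewhere the article gives iron a central place in the rationale:

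- The Fig. 1 legend states: "Ferric citrate inhibits two stimuli of FGF23 production, dietary phosphate absorption and iron deficiency".
- The section FGF23 production says that iron deficiency, described there as common in children with CKD, "may represent a novel factor contributing to elevated intact FGF23 levels in CKD".
- Table 4 requires "Serum ferritin < 500 ng/ml and transferrin saturation < 50" (per cent) for entry, so both values exist for every randomised child before treatment.
- Table 3 lists "Increased serum transferrin saturation -Increased serum ferritin" among the secondary endpoints, each compared from baseline.

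The same section, FGF23 production, also limits what is known: "Associations between iron status and intact FGF23 levels have not been specifically evaluated in large CKD cohorts". The human CKD association it reports is for total FGF23, whereas the primary outcome is intact FGF23.

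On power, the article reports that "a sample size of 160 participants provides 80% power to detect a treatment difference of 26% between treatment vs. placebo".

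**The concern.** Under the trial's own mechanism, two children with the same baseline iFGF23 need not follow the same course if one is iron-deficient and the other replete. Part of the first child's level is driven by a stimulus the drug may remove. Baseline iFGF23 records the starting level but not how much of it can be removed in this way.

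Entry criteria cap iron status at the top (ferritin below 500 ng/ml, TSAT below 50%) and set no floor, so children may range from frank deficiency to well replete. If iron status predicts iFGF23 in months 6–12 beyond the current covariates, that variation stays in the error term, and a chance difference between arms in iron status is not adjusted for. The design is set at 80% power with 20% loss to follow-up assumed, so a free gain in precision would be welcome.

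**Working it through.** **Inputs from the article.** N = 160; power 80%; difference 26%; analysis on the natural-log scale; alpha at the final analysis 0.0492, from "assigning an alpha of 0.0054 to the midpoint analysis, and 0.0492 to the final analysis"; 20% lost by month 12.

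**Assumptions.** 1:1 allocation, a two-sided test, one summary value per child for months 6–12, and 26% read as a ratio of 0.74. The partial R² of baseline iron is not in the article and is shown over a range.

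**1. The plan's own figure.** The 80% comes from a simulation whose standard deviations are not printed, so it can only be solved backwards.

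- Design effect: −ln(0.74) = 0.301.
- Implied SE: 0.301 / (1.967 + 0.842) = 0.107.
- Implied adjusted SD: 0.107 × √(n/2) = 0.678 with 80 per arm, or 0.607 with 64 per arm (after 20% loss).

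This neither confirms nor refutes the stated power.

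**2. Gain from a further covariate.** The SE is multiplied by √(1 − R²), so power = Φ[(1.967 + 0.842)/√(1 − R²) − 1.967]. The SD and the number per arm cancel. Equivalent N is 160 × (1 − R²), rounded up.

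| Assumed partial R² | Power | Equivalent N for 80% | Detectable reduction |
|---|---|---|---|
| 0 | 80.0% | 160 | 26.0% |
| 0.01 | 80.4% | 159 | 25.9% |
| 0.02 | 80.8% | 157 | 25.8% |
| 0.05 | 82.0% | 152 | 25.4% |
| 0.10 | 84.0% | 144 | 24.9% |

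**3. How much might remain after baseline iFGF23?** Write I for baseline iron, B for baseline iFGF23 and Y for follow-up iFGF23. The partial correlation is (r_IY − r_IB·r_BY) / √[(1 − r_IB²)(1 − r_BY²)]. Illustrative values are r_BY 0.6–0.8 and r_IB 0.2–0.4, with r_IY running from r_IB·r_BY (iron acts wholly through baseline) up to r_IB.

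- Lower end: r_IY = r_IB·r_BY gives partial R² = 0.
- Upper end: r_BY = 0.6 and r_IB = r_IY = 0.4 give (0.40 − 0.24)/√(0.84 × 0.64) = 0.218, so partial R² = 0.048.

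The gain is then about 0 to 2 percentage points of power.

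**4. Chance imbalance.** With 80 per arm, the SE of the between-arm difference in standardised iron is √(2/80) = 0.158, so a 1.96-SE imbalance is 0.31 SD. The shift in the estimate is 0.678 × √R² × 0.31:

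- R² = 0.01: 0.021, or 7% of the design effect.
- R² = 0.05: 0.047, or 16% of the design effect.

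**5. Iron as an effect modifier.** Suppose 40% of children are iron-deficient and their log change differs by 0.3 (both assumed). The 95% range of the chance imbalance is ±1.96 × √(2 × 0.4 × 0.6/80) = ±15.2 percentage points.

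| | 0.3 in both arms | 0.3 in the ferric citrate arm only |
|---|---|---|
| Average slope | 0.3 | 0.15 |
| Variance explained | 0.3² × 0.24 = 0.0216 | 0.15² × 0.24 = 0.0054 |
| Partial R² (÷ 0.678²) | 4.7% | 1.2% |
| Shift at 15.2 points | 0.3 × 0.152 = 0.046 | 0.15 × 0.152 = 0.023 |
| Share of 0.301 | 15% | 8% |

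The second column is nearer to the mechanism described in the article. There the power is about 80.5%.

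**The case against.** The strongest reply is that nothing here is an error. The model adjusts for the baseline value of the outcome and for every stratification factor, which is a sound randomised analysis. Leaving out one more prognostic variable neither biases the comparison nor inflates type I error. The evidence that iron predicts intact FGF23 is, by the article's own account, undeveloped, and every input to the size of the gain beyond the design figures is assumed. The 0.3 used in step 5 is as large as the whole design effect. Children already on iron therapy may enter if doses have been stable for two weeks before screening, so a deficient child on placebo need not stay deficient. A supporting interaction is also something an article may leave to the analysis plan.

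All of this stands as a limit on size. It does not show that the adjustment would do harm, and the covariate list in question is one the article itself states.

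Three stronger readings might be inferred, and the documents support none of them:

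- **That the primary estimate is biased.** A chance imbalance in iron is ordinary sampling error already inside the SE. Even a shift of 0.046 is 0.43 of the implied SE of 0.107.
- **That iron is the main effect modifier and precision is certainly lost.** The section FGF23 production treats dietary phosphate absorption as the central stimulus and speaks of iron only as a possible contributor.
- **That iron should have been a stratifier.** With 12 sites, two CKD stages and, if urine protein/creatinine has two levels (assumed), there are already 12 × 2 × 2 = 48 strata for 160 children, about 3 each. A fourth factor would make them sparser.

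**Conclusion.** The point holds as a modest, low-cost improvement to a valid analysis. The trial names iron deficiency as a target, has TSAT in hand before randomisation, and does not use it in the primary model. Some precision and some protection against chance imbalance may be forgone.

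At an assumed partial R² of 1–5%, power moves from 80% to about 80.4–82%. A gain to 84% needs 10%, which lies above the illustrative range of 0 to 4.8%. The result rests on 1:1 allocation, a two-sided test and one summary value per child for months 6–12. The documents give no figure for the residual association, so the true gain could be close to nil.

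**What to change.** Before unblinding, add baseline TSAT (continuous) to the primary model as one prespecified fixed covariate. Leave the months 6–12 treatment contrast and the stratification factors as they are. Optionally, prespecify a treatment-by-baseline-TSAT interaction as a supporting analysis: a main-effect covariate addresses prognostic imbalance, and only the interaction speaks to effect modification.

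The cost is one degree of freedom in the primary model and a line in the analysis plan. No new measurements, visits or participants are needed.

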The primary study hypothesis of the FIT4KiD trial is that compared to placebo, active treatment with ferric citrate will lower serum iFGF23 concentrations, measured over time (Table 3). To test this hypothesis, the FIT4KiD trial will recruit 160 pediatric participants between the ages of 6 and 17 years with CKD stages 3–4 (Table 4). After providing informed consent, study participants will be randomized to treatment with a weight-based dose of ferric citrate or treatment with placebo and will be followed for 12 months (Fig. 2). Participants weighing less than 31 kg will receive 3 g/day of ferric citrate; participants weighing greater than 31 kg but less than 51 kg will receive 5 g/day of ferric citrate; and participants weighing 51 kg or more will receive 6 g/day of ferric citrate. The total daily dosage will be divided into three doses to be taken with meals. Weight-based dosing was chosen instead of age-based dosing given that children with CKD are frequently small for age. Additionally, since dietary phosphate intake correlates with dietary caloric intake, and the latter correlates with body weight, weight-based dosing will best approximate dietary phosphate intake.

**Table 3 Tab3:** Ferric Citrate and Chronic Kidney Disease in Children (FIT4KiD) study hypotheses. *FC*, ferric citrate; *FGF23*, fibroblast growth factor 23

Primary endpoint
Compared to placebo, from baseline, active treatment with FC will lower serum intact FGF23 concentrations

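### The interim look is tied to 3-month completion or a calendar quarter, but its fixed O'Brien-Fleming alphas suit only 50% information on the months 6–12 test

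*Protocol article*

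**What the plan says.** All the relevant statements stand together in the protocol article, section *The FIT4KiD trial*, in the primary-analysis paragraph below Fig. 2.

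- Model: "Time will be modeled as two periods, months 1–3 and months 6–12".
- Primary inference: "with the primary test based on the difference between treatment arms during the second time period", that is, months 6–12.
- Interim timing: the single "interim analysis will be performed at 50% completion of 3 months of treatment or the first quarter of year 3" of the trial.
- Boundary: O'Brien-Fleming rules, "assigning an alpha of 0.0054 to the midpoint analysis, and 0.0492 to the final analysis".

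The next paragraph, on power, assumes that the treatment effect builds up linearly to month 3 and then stays level. It also assumes that "20% of participants would be lost to follow-up by month 12". Each participant "will be followed for 12 months".

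**The concern.** A fixed two-look O'Brien-Fleming pair belongs to one information fraction. Calling the interim the midpoint means half the information on the statistic tested at the end, which here is the months 6–12 arm difference. The 3-month trigger counts people who have finished the first modelled period, and someone who has just reached month 3 has no observation in the primary window. The alternative trigger is a calendar quarter and has no fixed link to information. The article joins the two with an *or* and does not say which governs.

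The early conservatism that motivates an O'Brien-Fleming boundary is at stake. If the look falls below 50% information, 0.0054 is easier to cross than an O'Brien-Fleming rule would allow. A crossing would also rest largely on early follow-up, in a trial whose primary window was chosen to reflect months 6–12.

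**Working it through.** **Inputs from the article:** N = 160; alphas 0.0054 and 0.0492; primary window months 6–12; 20% loss by month 12; the two triggers.

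**Assumptions, because the article gives no values:** two-sided alphas; 50% completion means 80 of 160; uniform accrual over A months; visits at months 1, 2, 3, 6, 9 and 12; random participant intercept with residual within-participant correlation ρ; site effects ignored.

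**1. The stated pair.** Two-sided 0.0054 gives z = 2.782, and 0.0492 gives z = 1.967. O'Brien-Fleming critical values follow z = c/√t, so the implied interim fraction is t = (1.967/2.782)² = 0.50 (the z ratio is 1.4145, or √2). The pair is therefore built for 50% information. Solving the standard two-look design for overall 0.05 gives c = 1.977 and alphas 0.0052 / 0.0480, so the stated pair is not reproduced exactly. Its overall error at t = 0.5 is 0.0513.

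**2. Who has primary-window data at the 3-month trigger.** The 80th participant completes month 3 at time A/2 + 3. The share followed for at least f months is (A/2 + 3 − f)/A, with a floor of zero. For f = 6 this is 0.5 − 3/A; for f = 12 it is 0.5 − 9/A. Before dropout:

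| Accrual A (months) | Any month-6 data | Complete to month 12 |
|---|---|---|
| 12 | 25% (40 of 160) | 0% |
| 24 | 37.5% (60) | 12.5% (20) |
| 36 | 42% (66–67) | 25% (40) |

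Under uniform accrual the month-6 share is always below one half.

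**3. Information on the months 6–12 contrast.** This is the final-analysis variance of the period-2 arm difference divided by its interim variance, by generalised least squares with 20% dropout. Months 1–3 data contribute through the random intercept.

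| A | ρ = 0.3 | ρ = 0.5 | ρ = 0.7 | ρ = 0.9 |
|---|---|---|---|---|
| 12 | 0.15 | 0.21 | 0.31 | 0.50 |
| 24 | 0.33 | 0.39 | 0.46 | 0.54 |
| 36 | 0.39 | 0.44 | 0.48 | 0.53 |

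The paragraph also names the treatment-by-time interaction as the term for inference. Read as the period-2 minus period-1 contrast, the fraction is 0.13–0.41 over the same accrual range, for ρ from 0 to 0.9.

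**4. Calendar trigger.** The first quarter of year 3 is taken as trial months 24–27. With ρ = 0.5, accrual over 18–36 months and enrolment opening at trial month 0–12, t runs from about 0.16 to 0.98.

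**5. Matching interim alpha below 50%.** Three O'Brien-Fleming forms were compared with 0.0054:

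| Form | t = 0.375 | t = 0.30 |
|---|---|---|
| Classical shape, 2[1 − Φ(1.977/√t)] | 0.00124 (4.3 times looser) | 0.00031 (about 18) |
| Lan-DeMets, two-sided 0.05, 2[1 − Φ(1.960/√t)] | 0.00137 (3.9) | 0.00035 (about 16) |
| Lan-DeMets, two one-sided 0.025, 4[1 − Φ(2.2414/√t)] | 0.00050 (about 11) | 0.000085 (about 63) |

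**6. Overall error if the stated pair is kept.** This is 1 − P(|Z₁| < 2.782, |Z₂| < 1.967) with correlation √t:

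- t = 0.50: 0.0513
- t = 0.375: 0.0521
- t = 0.25: 0.0529
- t = 0.15: 0.0535

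The rise due to timing is at most 0.0535 − 0.0513 = 0.0022 over this range. Whatever the timing, error cannot exceed 0.0054 + 0.0492 = 0.0546.

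**The case against.** The strongest reply has four parts.

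- **The shortfall is not a fact of the plan.** Accrual, visit months and correlation are not in the article. The mixed model borrows from months 1–3, and with high correlation the look reaches about 50%. This stands. A reader might infer that the interim is certainly well short of half the information, and the documents do not support that. They support only that nothing ties the look to half.
- **The error effect is small.** This stands too. The stated pair already gives 0.0513 at exactly 50%, timing adds at most about 0.002 in the range examined, and 0.0546 is a hard ceiling. A reading of serious type I error inflation is not supported. Nor is a single large multiplier for the looseness, which depends on both t and the boundary form.
- **The two triggers may describe the same expected date.** That is plausible, and it would make the extreme accrual cases unlikely. It still leaves the date unlinked to months 6–12 information. For the calendar trigger even the direction is unknown, so it cannot be said to come too early; it may come well after 50%.
- **The full protocol, analysis plan or monitoring-board charter may settle the details.** This is fair for the unstated details. It does not remove the mismatch, because the article itself fixes the trigger, the primary window and the numerical alphas, and these do not fit together.

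A reader might also infer that the interim will test months 1–3 instead. The article does not say so, and the point does not rely on it.

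**Conclusion.** The concern holds in a limited form. The article applies a boundary valid at 50% information on the months 6–12 test to a look set by 3-month completion or by calendar. At the 3-month trigger, information is below half for correlations of 0.3–0.7 under 12- to 36-month uniform accrual, and about half at 0.9. Where it is below half, the O'Brien-Fleming conservatism is weakened: slightly near 0.46 (about 1.5 times on the classical shape, 0.0054 against 0.0036) and substantially at 0.30–0.375. The practical risk is stopping on mostly short-term data at too lenient a threshold, rather than a material loss of type I error control. It should be fixed before any unblinded look, but it does not undermine the final analysis. The information fractions rest on the assumed accrual pattern, visit months and correlation. The mismatch between trigger, primary window and alphas does not.

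**What to change.** In the analysis plan and the monitoring-board charter:

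1. Define the interim test as the months 6–12 arm contrast from the primary model.
2. State one governing trigger. If both stay, say whether the earlier or the later applies.
3. Replace the fixed pair with a Lan-DeMets O'Brien-Fleming-type spending function at overall two-sided 0.05, evaluated at the information fraction actually reached on that contrast. Name the exact form, because the forms differ.

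Alternatively, move the look to 50% of months 6–12 information and still use the spending function, since the fraction will not be exactly 0.50.

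The cost is mainly wording. If the present timing is kept, the interim threshold will usually be stricter, so an early stop becomes less likely; if the look is moved, it comes later. With the two one-sided 0.025 form, the final alpha stays at about 0.049–0.050 when the interim falls at or below about 50% information (0.0031 / 0.0490 at exactly 50%). It is lower if a calendar trigger puts the look later. The two-sided form spends more at the interim (0.0056 at 50%) and leaves about 0.048 for the final test. A spending function also removes the 0.0513 that the stated pair carries even at its nominal midpoint.

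### The stated interim and final alphas (0.0054 and 0.0492) give an overall two-sided type I error of 0.0513 at half the information, not the presumed 0.05

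*Protocol article*

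**What the plan says.** The point is in the protocol article, section The FIT4KiD trial, in the paragraph on the primary analyses after Fig. 2. One interim look is planned: "A single interim analysis will be performed at 50% completion of 3 months of treatment or the first quarter of year 3 of the trial". Its boundary is named as O'Brien-Fleming, and two numeric thresholds are fixed: "assigning an alpha of 0.0054 to the midpoint analysis, and 0.0492 to the final analysis". The final threshold applies to the months 6–12 contrast, "with the primary test based on the difference between treatment arms during the second time period".

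The paragraph gives neither the overall alpha nor whether the tests are one- or two-sided. It does not mention a spending function or recalculation of the boundary at the information actually observed.

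**The concern.** O'Brien-Fleming boundaries for one midpoint look and a final analysis are standard, and at an overall two-sided 0.05 they are 0.0052 and 0.0480. Both printed values are larger than these. When both thresholds of a pair are looser than those of a boundary that uses exactly 5%, the pair must use more than 5%.

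This matters because these are the decision thresholds for the primary endpoint. A final p-value between 0.0480 and 0.0492 would be reported as a positive trial under a rule whose overall error exceeds the presumed level. Such a result would be open to challenge, and the threshold could not credibly be changed after unblinding.

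**Working it through.** **Inputs from the article**

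- Interim alpha 0.0054 and final alpha 0.0492.
- One interim look, called the midpoint, so the information fraction is taken as t = 0.5.
- Assumed, because not stated: overall alpha 0.05, two-sided.

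**Step 1. Convert to z.** With z = Φ⁻¹(1 − α/2), 0.0054 gives z₁ = 2.782 and 0.0492 gives z₂ = 1.967. The ratio is 2.782/1.967 = 1.4145, about √2. A two-look O'Brien-Fleming boundary at t = 0.5 has z₁ = c√2 and z₂ = c, so the stated pair has that shape, with c about 1.967.

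**Step 2. Overall error of the stated pair.** Under the null hypothesis the two test statistics are bivariate normal with correlation √t = √0.5, and

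overall α = 1 − P(|Z₁| < 2.782 and |Z₂| < 1.967).

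Numerical integration gives **0.05129**. A simulation of 20 million draws gives 0.0513. The plain sum of the alphas, 0.0546, is not the right comparison because it ignores the correlation.

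**Step 3. Could rounding explain it?** Moving the two alphas over their rounding ranges (0.00535 to 0.00545, and 0.04915 to 0.04925) moves the overall error only between 0.0512 and 0.0514. It does not reach 0.05.

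**Step 4. Which pairs hold 0.05 at t = 0.5?**

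| Rule | Interim | Final |
|---|---|---|
| Exact O'Brien-Fleming (c = 1.9774; z = 2.797 and 1.977) | 0.0052 | 0.0480 |
| Lan-DeMets O'Brien-Fleming-type spending | 0.0031 | 0.0490 |
| Same spending function applied directly with two-sided 0.05 | 0.0056 | 0.0478 |
| Interim kept at 0.0054 | 0.0054 | 0.0479 |
| Final kept at 0.0492 | 0.0026 | 0.0492 |

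None of the standard rules tried gives 0.0054 with 0.0492.

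**Step 5. Other readings of the stated pair.** Read as one-sided alphas at t = 0.5, the overall error is 0.0509. As a two-sided pair at other information fractions:

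| t | 0.25 | 0.3 | 0.4 | 0.5 | 0.6 | 0.7 | 0.8 |
|---|---|---|---|---|---|---|---|
| Overall α | 0.0529 | 0.0526 | 0.0520 | 0.0513 | 0.0506 | 0.0500 | 0.0495 |

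The excess disappears only from about t = 0.70 upwards.

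**Step 6. Power cost of correcting the final threshold.** In a simple normal approximation with 80% power at two-sided 0.0492, the standardized effect is 1.967 + 0.842 = 2.808 (from unrounded values). At 0.0480 the critical value is 1.977, and power is Φ(2.808 − 1.977) = 79.7%.

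**The case against.** The strongest case on the other side is about consequence and interpretation, not arithmetic.

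- **Size.** The excess is 0.13 percentage points in a phase 2 biomarker trial of 160 participants. It affects the final decision only if p falls in a window 0.0012 wide. This stands: it is a small correction and no design choice turns on it.
- **Benchmark.** The article never states 0.05, so the mismatch is with a presumed level. This also stands as a caveat. But the pair lies so close to the standard two-sided 0.05 boundary that no other target is plausible, and the one-sided reading exceeds 0.05 too. If 0.0513 was intended, it is undeclared.
- **Source.** Both alphas come from one constant (z₁²/2 = 3.870, z₂² = 3.869; the exact value is 1.9774² = 3.910), so this is not a typing slip. The authors may have followed the reference that the article cites for the rule, which is not at hand. That could explain where the pair came from, but it does not change the error rate that the pair delivers.
- **Full protocol or SAP.** Either may recalculate the boundary at the observed information. That limits certainty about which threshold will finally be applied, but the printed numbers still need correcting.
- **Information fraction.** The pair 0.0052/0.0480 is exact only at t = 0.5; at t = 0.3 it too gives about 0.0513. This is a fair point about the remedy and is why a spending function is the better fix. It does not rescue the stated pair. The interim is triggered by 3 months of treatment or by a calendar date, while the test concerns months 6–12, so information on that contrast may well be below half, where the error is larger.

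**Conclusion.** The concern holds. As printed, 0.0054 and 0.0492 give an overall two-sided type I error of 0.0513 at half the information, 0.13 percentage points above 0.05. The conclusion assumes an intended overall two-sided 0.05 and jointly normal test statistics with t = 0.5. It survives rounding of the alphas and the one-sided reading, and it fails only if the interim carries about 70% or more of the final information. The error is modest, but it lies in a prespecified decision threshold for the primary endpoint, so it should be corrected.

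**What to change.** Before any unblinded look:

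1. State the overall alpha and whether the tests are two-sided.
2. Preferably, name an O'Brien-Fleming-type spending function and compute both boundaries at the information fraction actually reached for the months 6–12 contrast. This also covers an interim that does not fall at half the information.
3. If fixed thresholds at half the information are kept, print 0.0052 (interim) and 0.0480 (final). If 0.0054 is kept at the interim, use 0.0479 at the final.
4. Re-run the power simulation with the corrected final alpha.

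The change is two numbers or one added sentence, plus the re-run. By the approximation above, power falls from 80% to about 79.7%, so the sample size need not change.
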